# 2 Schema of the protocol

[figure not shown]

# 3 Concept sheet

| Primary Registry | Clinical Trial Registry of India (CTRI) |
| --- | --- |
| Contact for Public & scientific Queries | [name] [name], DM, Department of Medical Oncology, TMH  Email: [contact] |
| Scientific Title | MACE-CTRT : Metronomic Adjuvant Chemotherapy Evaluation in locally advanced head and neck cancers post radical chemoradiation |
| Countries of Recruitment | India |
| Health Condition Studied | Locally advanced head and neck cancers |
| Interventions | Arm A : Observation  Arm B : Oral metronomic chemotherapy for 18 months. Tab methotrexate 15 mg/m2 weekly PO and Capsule celecoxib 200 mg PO Twice daily |
| Aim | To study whether adjuvant treatment with metronomic chemotherapy leads to a betterment in outcome, in locally advanced head and neck cancers post radical chemoradiation |
| Objectives | Primary objective   1. To compare the overall survival at 3 years of adjuvant metronomic chemotherapy with that of observation in patients with locally advanced head and neck cancers post radical treatment   Secondary objectives   1. To compare the 3 year progression free survival of adjuvant metronomic chemotherapy with that of observation in patients with locally advanced head and neck cancers post radical treatment. . 2. To compare the grade 3-4 toxicity between adjuvant metronomic chemotherapy and observation 3. To compare the 6,12,18,24 & 36 months QOL score between the 2 arms |
| Population | **Key Inclusion criteria**   1. Participants must be post radical CTRT for a histologically confirmed squamous cell of head and neck region. 2. Participants must have no gross residual disease post 10-12 weeks of of completion of radical CTRT treatment . 3. Age : Any age above 18 years. No maximum age. 4. ECOG performance status ≤2 5. Participants must have normal organ and marrow function   **Key Exclusion criteria**   1. Participants who are receiving any other investigational agents. 2. Primary sites of malignancy major salivary gland or nasopharynx or skin 3. Patients with QTc prolongation defined as QTc interval greater than 480 ms |
| Study Type | 2 arm, parallel design, open label, superiority, explantory, integrated, sequential Phase3 with multiple interim , randomized controlled trial |
| Sample Size | Group sequential design sample size with 3 interim analysis for overall survival with sample size 1046. |
| Date of first enrollment | Post IRB approval and CTRI registration |
| Recruitment Status | Not opened |
| Outcome Measures | 1. 3 year OS : OS will be defined time in days between date of randomization to date of death. Patients alive at their last follow ups would be censored. The OS would be estimated by Kaplan meier analysis and would be compared between the 2 arms by the log rank test. Cox proportional hazard model would be constructed for calculation of hazard ratio. 2. 3 year PFS : PFS will be defined time in days between date of randomization to date of progression or death whichever is earlier. Patients who have not progressed or died at their last follow ups would be censored.The median PFS would be estimated by Kaplan meier analysis and would be compared between the 2 arms by the log rank test. Cox proportional hazard model would be constructed for calculation of hazard ratio. 3. Toxicity : To compare CTCAE version 4.03 worst grade toxicity between the 2 arms during any period of chemotherapy. Chi- square test or fisher's test would be used for comparison. The NCI Common Terminology Criteria for Adverse Events version 4 (NCI CTCAE v4.03) will be used to classify and grade the intensity of adverse events after each treatment cycle. 4. TOI ( Trial outcome index) : TOI will be calculated at baseline and at 6, 12,18,24,36 months in both arms from FACT Head and neck QOL proformas. Increment in TOI of 6 units would be considered significant. The proportion of patients showing an increment in TOI between the 2 arms would be compared by Proportion test. |
| Feasibility | Each year we treat 600 patients with CTRT. Hence if post CTRT each year even if we can recruit 120 patients than in 9 years the recruitment would be over. Hence this study is feasible. |
| Significance | Head and neck cancers are one of the most commonest cancers in the country. Most present locally advanced state. The current options produce unsatisfactory outcomes. Addition of oral metronomic chemotherapy in multiple retrospective studies has been associated with improvement in survival. Hence this study is planning to test this hypothesis. If successful this will be a cost effective and minimally toxic treatment option for patients. |
| Funding | Both intramural and extramural funding options will be explored |
| Risks | Oral metronomic therapy in the study conducted by Pai et al had no grade 3-4 side effects. Even in international studies the incidence of grade 3-4 side effects is below 5%. Hence this seems to be a safe option |

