# 7 Hypothesis & trial design

Adjuvant metronomic chemotherapy will result in a 6.5% absolute improvement in 3-year OS rate, which would be considered a clinically meaningful increase .

This will be a 2 arm, parallel design, open label, superiority, explantory phase III randomized controlled trial with multiple interim analysis.

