## 13.2 Rationale for interim analysis

The survival benefit shown with adjuvant metronomic studies is limited sample size cohort studies. Hence as the investigators plan to do a study which is powered for an absolute survival improvement of 6% at 3 year in OS.It was decided to have a multiple interim analysis.

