## 13.3 Sample size justification

### 13.3.1 Sample size

The primary endpoint for is 3 year OS. The study assumes a 3 year OS in standard arm of 69%. With Type I error of 5% , Type II error of 20%, for a hazard ratio of 0.77, with study duration of recruitment of 9 years, study follow up of 3 years and 5 % lost to follow up the sample size was calculated using fixed design, two-arm trial with time-to-event

outcome (Lachin and Foulkes, 1986) in Rstudio version 3.2.1. The sample size required was 950 patients with analysis done at 485 events. However in view of the large sample size 3 interim analysis were included in this study using Group sequential design sample size with Hwang-Shih-DeCani spending function for time-to-event outcome events. The final **sample size was 1038 patients**. The analysis plan below shows events at each analysis with the decision rules.

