**Decision rules**

Upper bound spending computations assume trial continues if lower bound is crossed.

----Lower bounds---- ----Upper bounds-----

Analysis N Z Nominal p Spend+ Z Nominal p Spend++

1st interim 133 -0.75 0.2275 0.0203 2.95 0.0016 0.0016

2nd interim 265 0.13 0.5509 0.0335 2.58 0.0049 0.0044

3rd interim 398 0.91 0.8180 0.0552 2.17 0.0151 0.0118

Final analysis 530 1.69 0.9548 0.0910 1.69 0.0452 0.0322

Total 0.2000 0.0500

+ lower bound beta spending (under H1):

Hwang-Shih-DeCani spending function with gamma = -2.

++ alpha spending:

Hwang-Shih-DeCani spending function with gamma = -4.

Boundary crossing probabilities and expected sample size

assume any cross stops the trial

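### The protocol gives two sample sizes (1046 and 1038) and two materially different target effects (6.5 and about 6 points), and its 485 events reproduce only for 69% versus 75%

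*Protocol*

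**What the plan says.** **Sample size.** The concept sheet (Protocol section 3) has a "Group sequential design sample size with 3 interim analysis for overall survival with sample size 1046". Section 13.3.1, for the same group sequential design with three interim analyses, says the final "sample size was 1038 patients". That section starts from a fixed design of 950 patients and 485 events. The decision-rules table puts the final analysis at 530 events.

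**Target effect.** Section 7 states: "Adjuvant metronomic chemotherapy will result in a 6.5% absolute improvement in 3-year OS rate", and calls this gain clinically meaningful. Section 13.2 describes a study "powered for an absolute survival improvement of 6% at 3 year in OS". Section 13.3.1 performs the calculation "for a hazard ratio of 0.77".

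**Other inputs.** Section 13.3.1: "The study assumes a 3 year OS in standard arm of 69" per cent; "With Type I error of 5% , Type II error of 20" per cent. It also gives 9 years of recruitment, 3 years of follow-up and 5% loss to follow-up. It states neither the sidedness of the type I error nor the allocation ratio.

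**The concern.** The number of patients to recruit and the effect the trial is sized to detect are core design figures, and each should have one value. Here the summary page and the sample size section disagree on the first. The hypothesis, the rationale and the calculation disagree on the second. A reader who enters the printed hazard ratio of 0.77 into the stated calculation does not recover the printed 485 events.

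At stake is whether the design can be reproduced, and whether a later reader can tell which gain the trial was built to detect: the one section 7 calls clinically meaningful, or a smaller one.

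**Working it through.** **Inputs.** Control 3-year survival 69%, type I error 5%, power 80%, 485 fixed-design events, 950 patients (section 13.3.1); 530 final events (decision-rules table). Assumptions not stated in section 13.3.1: two-sided test (z = 1.960), 1:1 allocation, proportional hazards.

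**Step 1: put the three effects on one scale.** HR = ln(S_exp)/ln(0.69).
- +6.5 points: ln(0.755)/ln(0.69) = 0.757
- +6 points: ln(0.75)/ln(0.69) = 0.7753
- HR 0.77: 0.69^0.77 = 0.7515, a gain of 6.15 points

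**Step 2: try to reproduce the 485 events.** Schoenfeld: events = 4 × (1.960 + 0.842)² / (ln HR)². Power at 485 events = Φ(|ln HR| × √485/2 − 1.960).

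| Target | HR | Events, Schoenfeld | Events, Freedman | Events, Lachin-Foulkes | Power at 485 events |
|---|---|---|---|---|---|
| +6 points | 0.7753 | 485 | 490 | 484 | 80.0% |
| HR 0.77 | 0.77 | 460 | 465 | 459 | 82.1% |
| +6.5 points | 0.757 | 407 | 412 | 406 | 86.4% |

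The plan's 485 is matched by 69% versus 75%. Lachin-Foulkes is the method the protocol names. With exponential survival, uniform accrual and 5% loss taken over 3 years (the time scale is not stated), it gives 484 events and 948 patients for 6 points, against the stated 485 and 950. The event count hardly moves with the loss assumption, so it is the better guide to which effect was used.

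**Step 3: sensitivity to sidedness.** At one-sided 5% (z = 1.645) the Schoenfeld counts are 382 (6 points), 363 (HR 0.77) and 321 (6.5 points). None is near 485, so the match in step 2 depends on reading the 5% as two-sided.

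**Step 4: the two totals.** Event inflation 530/485 = 1.0928, and 950 × 530/485 = 1038. The ratio 1038/950 = 1.0926 agrees with that inflation; 1046/950 = 1.101 does not.

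**Step 5: the alpha in the boundary table.** The final row reads "Final analysis 530 1.69 0.9548 0.0910 1.69 0.0452 0.0322". The upper-bound spend adds up to 0.0016 + 0.0044 + 0.0118 + 0.0322 = 0.0500. Numerical integration of the stated spending functions (gamma −4 upper, −2 lower, four equal looks, non-binding lower bound) gives:
- one-sided 0.05: upper bounds 2.95, 2.58, 2.17, 1.69, as printed; inflation 1.094
- one-sided 0.025: upper bounds 3.16, 2.82, 2.44, 2.01; inflation 1.087

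So the 485 events need two-sided 0.05 (one-sided 0.025), while the bounds built on them spend one-sided 0.05. With inflation 1.087, the same fixed design would end at about 485 × 1.087 = 527 events and 950 × 1.087 = 1033 patients.

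**The case against.** A reader might infer three competing targets. The figures do not support that. HR 0.77 and 6 points differ by 0.15 points, and 0.77 is probably 0.7753 cut to two decimals (it would round to 0.78). Only about 6 points and 6.5 points differ materially.

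A reader might also infer that the trial is underpowered for its own hypothesis. On the two-sided reading the reverse holds: sizing for 6 points gives 86% power for 6.5 at 485 events.

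Nor do the documents support the inference that the unclear target lets the result be judged either way. The primary comparison is a log-rank test (section 11.1) against fixed Z bounds, and the target effect does not enter that decision.

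The gap of 8 patients is 0.8%. The analyses are set by event counts, and the accrual described in the concept sheet (120 a year for 9 years, 1080 in all) covers both totals. Section 7 can also be read as stating what gain matters clinically, with section 13.2 stating what the trial is powered for.

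All of this stands, and it limits the consequence. It does not remove the conflict: nothing in the protocol explains 1046, rounding cannot turn 6 into 6.5, and section 7 does not say that the trial is sized for a different gain.

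**Conclusion.** The inconsistency is real and sits in the current text. One stated sample size does not follow from the calculation, and neither the hypothesised gain nor the printed hazard ratio reproduces the stated 485 events. HR 0.77 needs about 5% fewer events (460) and 6.5 points about 16% fewer (407). The practical effect is small and conservative, with power of 80% to 86% at 485 events across the stated targets. This rests on two-sided 5%, 80% power, 1:1 allocation and proportional hazards; the first and third are assumptions.

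It is tempting to conclude that 1038 patients and 530 events are therefore the correct figures. The documents do not support that either. The agreement of 1038 with 950 × 530/485 shows only that patients and events were inflated by the same factor. The fixed design and the boundary table use different alpha levels, so neither final figure is settled until that is resolved.

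**What to change.** 1. State one sample size in sections 3 and 13.3.1: 1038 if the section 13 calculation stands, otherwise show how 1046 arises.
2. In section 13, state the design effect that gives 485 events (69% versus 75% at 3 years, HR 0.775), together with the sidedness of alpha and the allocation ratio.
3. Either align section 7 with that effect, or keep 6.5 points as the clinically meaningful gain and say that the trial is sized for 6 points, giving the power for 6.5 (86% at 485 events, two-sided). Which gain counts as clinically meaningful is the investigators' decision and cannot be settled by arithmetic.
4. Confirm the final patient and event numbers when the alpha of the fixed design and of the boundary table is reconciled.

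Items 1 to 3 cost amendment wording only. Item 4 needs the group sequential calculation to be rerun and may change the bounds and, to some extent, the final numbers.

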# 4 Background

## 4.1 Outcomes post chemoradiation in locally advanced head & neck cancers

Locally advanced head and neck cancers have poor survivals. The 2 year , 5 year and 10 year overall survival post standard fractionation radiation are 45.6%, 29.3% and 18.3% respectively ( Beitler et al, RTOG 9003).[^1^](https://paperpile.com/c/3p5DlQ/bqQo) The addition of concurrent chemotherapy to radiation leads to an improvement in survival. The 2 year and 5 year overall survival post concurrent chemoradiation are 55 % and 33.7 % in accordance with the MACH-NC analysis .[^2^](https://paperpile.com/c/3p5DlQ/UonL) Even when chemoradiation is done for larynx preservation the overall survivals are at the best modest. The results of RTOG 99-11 revealed a 5 year and 10 year overall survival rate of 55.1% and 27.5%.[^3^](https://paperpile.com/c/3p5DlQ/KRwY)

## 4.2 Failure pattern post radical chemoradiation

The temporal profile of the failure rates reveals that 60% of failures happen in first 2 years.[^2^](https://paperpile.com/c/3p5DlQ/UonL) The sites of failure is predominantly still loco-regional. Around 40% of failures are local, 25% are regional and 35% have both local and regional failures. In these patients 35% of the patients have systemic disease as the site of failure.[^4, 5^](https://paperpile.com/c/3p5DlQ/rA0d+uWju)

## 4.3 Ineffective efforts & need for a new strategy

Strategies to improve upon these outcomes of concurrent chemoradiation have failed. Addition of multiple chemotherapeutic drugs as sensitizer over single agent platinum is not useful.[^2^](https://paperpile.com/c/3p5DlQ/UonL) Similarly addition EGFR receptor inhibitors like cetuximab or panitumumab to concurrent cisplatin and standard fraction radiation too failed to improve outcomes.[^6, 7^](https://paperpile.com/c/3p5DlQ/YoMw+XwPE) The efforts towards modification of fractionation of radiation along with concurrent chemotherapy have also failed.[^8^](https://paperpile.com/c/3p5DlQ/qj7q) Hence at present concurrent cisplatin and standard fraction radiation is considered as the standard of care treatment in locally advanced oropharyngeal cancers and larynx preservation option in locally advanced laryngo-pharyngeal malignancies.[^9, 10^](https://paperpile.com/c/3p5DlQ/avBW+SSSs)

Newer strategies are urgently warranted to improve upon the outcomes in head and neck cancers. Sequencing efforts and integrative genomics have revealed a great deal about the molecular abnormalities that underlie HNSCC. Unfortunately, they have also demonstrated marked heterogeneity, which will make optimizing therapeutic intervention difficult. In HNSCC, oncogenic mutations are rare and mutations in tumor suppressor genes dominate. Restoring function of a tumor suppressor pharmacologically is difficult.[^11^](https://paperpile.com/c/3p5DlQ/SOv7)

## 4.4 In Vivo data for metronomic

In advanced solid tumors it's proposed that adjuvant treatment with metronomic chemotherapy in preclinical mouse models limits metastatic spread.[^12^](https://paperpile.com/c/3p5DlQ/kaGd) A considerable percentage of HNSCC overexpress anti-apoptotic Bcl-2 proteins and that high levels of Bcl-2 correlates with resistance to platinum-based chemotherapy and thus with a poor prognosis.[^13^](https://paperpile.com/c/3p5DlQ/tV25) Imai et al. have demonstrated that ( Metronomic chemotherapy) MC, in association with taxotere decreased both tumor mitotic index and microvessel density and increased survival of mice bearing HNSCC xenografts. Authors evaluated the combination AT101/taxotere on the survival of endothelial cells and HNSCC also in vitro. They observed an additive toxicity for endothelial cells and a synergistic toxicity for tumor cells. Authors concluded that, based on these results, HNSCC patients might benefit from metronomic chemotherapy regimen.[^14^](https://paperpile.com/c/3p5DlQ/ZgMr)

## 4.5 Metronomic chemotherapy : Clinical efficacy data in adjuvant setting

In a study by Lin et al cohort consisted 80 patients with advanced head and neck cancer treated between January 2003 and December 2007. Half of the patients received oral UFUR as metronomic adjuvant chemotherapy, while the other half received no treatment.The disease-free survival rates at 4 years were 84.6% with oral UFUR treatment and 60.9% without UFUR therapy (P = 0.02). The authors concluded that metronomic adjuvant chemotherapy regimen seems a promising option.[^15^](https://paperpile.com/c/3p5DlQ/SBHF)

Similar to this Oral metronomic chemotherapy (OMCT) consisting of methotrexate and celecoxib has shown promise in Perioperative and adjuvant setting in TMH too. Treatment of locally advanced head and neck cancers with adjuvant metronomic chemotherapy post surgery and RT has shown to decrease failure rates and tends to improve upon the survival. In a retrospective review done by Pai et al of advanced T3/T4 head and neck cancers adjuvant OMCT improved the disease free survival by 14.9%. OMCT administered for 18 months seems to have potential for improving outcomes in locally advanced head and neck cancers post radical chemoradiation .[^16^](https://paperpile.com/c/3p5DlQ/0Afq)

In a retrospective review of fifty two head and neck cancer patients done by Furusaka et al metronomic S1 was given for 2 years as adjuvant. Forty-three patients (82.7%) were able to complete the chemotherapy for 2 years without dose reduction. The 3-year disease-free survival rate and 3-year survival rate were 82.6% and 94.0%, respectively.[^17^](https://paperpile.com/c/3p5DlQ/Pw7r)

Similarly in advanced nasopharyngeal cancers too MCT has been evaluated post comple treatment.The study population consisted of 625 NPC patients with available pEBV ( plasma EBV ) DNA levels before and aftertreatment. Eighty-five patients with persistently detectable pEBV DNA after 1 week of completing radiation therapy were eligible for this retrospective study. Of the 85 patients, 33 were administered adjuvant chemotherapy consisting of oral tegafur-uracil (2 capsules twice daily) for 12 months with (n=4) or without (n=29) preceding intravenous chemotherapy of mitomycin-C, epirubicin, and cisplatin. The remaining 52 patients who did not receive adjuvant chemotherapy served as the control group. The adjuvant oral metronomic chemotherapy (OMCT) has been associated with a remarkable improvement in overall survival at 5 years from 27.6% to 71.6%.[^18^](https://paperpile.com/c/3p5DlQ/XaIp)

## 4.6 Toxicity profile of metronomic therapy when used as adjuvant

Adjuvant OMCT has been found to be safe and tolerable. There were no grade 3-4 toxicity associated with OMCT in the study reported by Pai et al . In the study reported by Furusuka et al only two patients (3.8%) had of grade 3- hematological toxicity was noted. In the report of Twu et al only 1 incident of transient of transient leucopenia was seen 93.3%) .

# 5 Rationale for the study

OMCT seems to improve survival when administered as adjuvant treatment in locally advanced head and neck cancers. This therapy is associated with no major grade 2-4 toxicity. Hence we have planned this study to assess the efficacy of adjuvant OMCT (consisting of weekly methotrexate and celecoxib) in locally advanced head and neck cancers post radical chemoradiation.

# 6 Aims & Objectives

## 6.1 Aim

To study whether adjuvant treatment with metronomic chemotherapy leads to a betterment in outcome, in locally advanced head and neck cancers post radical chemoradiation

## 6.2 Objective

### 6.2.1 Primary objective

To compare the 3 year overall survival of adjuvant metronomic chemotherapy with that of observation in patients with locally advanced head and neck cancers post radical chemoradiation .

The primary endpoint would be 3 year overall survival.

### 6.2.2 Secondary objectives

1. To compare the 3 year progression free survival of adjuvant metronomic chemotherapy with that of observation in patients with locally advanced head and neck cancers post radical chemoradiation . The secondary endpoint would be 3 year progression free survival.
2. To compare the grade 3-4 toxicity between adjuvant metronomic chemotherapy and observation
3. To compare the 6,12,18,24 & 36 months QOL scores between the 2 arms

# 7 Hypothesis & trial design

Adjuvant metronomic chemotherapy will result in a 6.5% absolute improvement in 3-year OS rate, which would be considered a clinically meaningful increase .

This will be a 2 arm, parallel design, open label, superiority, explantory phase III randomized controlled trial with multiple interim analysis.

# 8 Study setting

The proposed study will be conducted at head and neck medical oncology department of TMC. Both patients from TMH and ACTREC would be recruited.

# 9 Eligibility criteria

## 9.1 Inclusion criteria

1. Participants must be post radical chemoradiation for a histologically confirmed stage III-IV squamous cell cancers of the head and neck region.
2. Participants must have no gross residual disease post of completion of CTRT
   1. Assessment for same would be done in accordance with institutional standards at a visit post 10-12 weeks of completion of CTRT by PET CT
3. Participants must have malignancy arising from one of the following sites pharynx ( inclusive of oropharynx, hypopharynx) or larynx ( inclusive of supraglottis, glottis and subglottis).
4. Age : Any age above 18 years. No maximum age.
5. ECOG performance status ≤2
6. Participants must have normal organ and marrow function as defined below:
   1. Leukocytes ≥3,000/mcL
   2. Platelets ≥100,000/mcL
   3. Total bilirubin < 1.5 × institutional upper limit of normal
   4. AST(SGOT)/ALT(SGPT) ≤2.5 × institutional upper limit of normal
   5. Calculated Creatinine clearance > 30 ml/min
7. The effects of oral metronomic chemotherapy ( inclusive of methotrexate) on the developing human fetus are teratogenic. Hence women of childbearing potential and men must agree to use adequate contraception (hormonal or barrier method of birth control; abstinence) prior to study entry and for the duration of study participation. Should a woman become pregnant or suspect she is pregnant while she or her partner is participating in this study, she should inform her treating physician immediately. Men treated or enrolled on this protocol must also agree to use adequate contraception prior to the study, for the duration of study participation, and 6 months after completion of protocol.
8. Both men and women of all races and ethnic groups are eligible for this trial.
9. Willing and able to comply with all study requirements, including treatment (able to swallow tablets), able to be followed up at regular intervals and/or nature of required assessments (e.g. able to have IV contrast if this is required for tumour assessments)
10. Ability to understand and the willingness to sign a written informed consent document

